### 2.3. Interventions

To implement this protocol, it will be necessary to include a physical exercise graduate in the multidisciplinary group (described in Section 2.1), who will design and conduct the intervention. This will ensure that patients are controlled, monitored, and directed by a specialist at all times, thus guaranteeing the safety of the protocol and optimizing the intervention.

The intervention program will be conducted over a period of 8 weeks, with three one-hour sessions/week. Every session will comprise a warmup, the main intervention, and a cooldown. The warmup and cooldown will last 10–12 min, respectively, and will be based on the dynamic mobilization of the main muscle groups, especially those of the lower body, to prepare and recover them, respectively, for the main part of the intervention. In the main part, lasting 30–35 min, aerobic-based exercise will be implemented. To reduce mechanical limitations while carrying out the exercise, both a treadmill and a cycloergometer will be used, rotating them weekly, as recommended by a recent meta-analysis [34]. Motivational strategies, such as playing music during the session and giving messages of encouragement, will be used by the professionals supervising the activity. The periodization of the intervention will include two training periods: a two-week familiarization period (FP) and a 6-week training period (TP). The FP will be common to both groups and will be used to increase the training intensity gradually to prepare the patients for the high-intensity TP. In the TP, each group will carry out the corresponding intervention. The HIIT-G group will train according to a predefined high-intensity training program. Taking into account that VO_2_ can be improved either with short or long HIIT intervals [9] and that patients are expected to be in poor physical condition, short training intervals of 1′30′′ will be combined with active rest periods. In each session, the work time at the determined intensity will be at least 50% of the total work interval. The training interval intensity will be gradually increased as the rest periods are reduced. In accordance with Taylor et al. (2017) [35], both the maximal heart rate and the subjective perception of effort will be controlled. The HIIT-G training periodization is presented in more detail in Table 1.

The training prescribed to the HRV-G group will depend on the subjects’ daily HRV and will follow the HRV-training schema designed by Kiviniemi et al. (2007) [36] (Figure 1). The HRV registration procedure and analysis are described by Carrasco-Poyatos et al. (2020) [37], although, in accordance with the results from recent randomized controlled trials [38,39] and the characteristics of the sample, only high or low intensity will be considered for the present protocol.

The assigned study intervention will be modified or discontinued if the drug dose changes in response to harms, the participant requests it, the disease worsens, or the cardiologist recommends it. Compliance with the exercise protocol will be controlled by the nurse.

### 2.4. Outcomes

The primary outcome of this study will be the peak oxygen uptake (VO_2peak_) obtained in an incremental treadmill test. The secondary outcomes will be treadmill endothelial and work parameters; heart rate variability; functional parameters; relative weight and body fat distribution; quality of life; inflammatory markers; cognitive function; and exercise adherence, feasibility, and safety. The treadmill test and blood sample collection will be carried out by the cardiologist one week before and after the intervention. Data on functional performance, relative weight and body fat distribution, quality of life, and cognitive function will be recorded by the multidisciplinary group during the first and last weeks of the exercise intervention. Heart rate variability, exercise adherence, feasibility, and safety will be recorded daily during the intervention by the physical exercise graduate.

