Therefore, HRV is a biomarker that can indicate the health status of the cardiovascular system, serving as an effective tool for individualizing the training load in cardiac patients. Moreover, it can be used to measure cardiovascular responses to therapeutic interventions, with HIIT-based exercise being the most recommended option. However, with the goal of obtaining improved results regarding cardiovascular rehabilitation, it is still unclear whether to opt for HIIT training or to individualize HIIT training using HRV. We hypothesize that (i) both HIIT training and HRV-guided training will improve cardiorespiratory fitness, functional performance, heart rate variability, relative weight and fat distribution, inflammatory markers, cognitive function, and quality of life in post-stroke patients but that HRV-guided training will achieve better results; and (ii) HRV-guided training will be safer and more feasible and will generate more patient adherence to the program. The primary objective of the proposed protocol is to determine the effect of HIIT- compared to HRV-guided training on cardiorespiratory fitness in post-stroke patients who undertake an 8-week cardiac rehabilitation program. The secondary aims of this trial are (i) to determine the effect of HIIT training compared to HRV-guided training on heart rate variability scores in post-stroke patients, (ii) to investigate the effect of each exercise program in terms of the adaptations obtained in functional parameters, body composition, and the quality of life of these patients, (iii) to study the effect of both programs on inflammatory markers, (iv) to determine which exercise program is more effective at improving cognitive function, and (v) to analyze whether the two exercise programs are equally feasible and safe, as well as to evaluate their effect on patient adherence to the cardiac rehabilitation program.

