#### 2.4.1. VO_2peak_

In accordance with the Spanish Cardiology Society, a modified version of the Bruce protocol will be used as the treadmill test, as it is indicated for elderly people and those considered high risk. Unlike the Bruce protocol, in the modified version, stage 1 starts at a 0% gradient, walking at 45.5 m/min. During stages 2 and 3 (at 3′ and 6′), the percentage gradient increases by 5% each time. Therefore, 6′ more exercise is performed at low intensity. From there, the percentage gradient will increase by 2% every 3′, and the walking speeds will be 67 m/min, 91 m/min, 112.5 m/min, and 136.8 m/min in Stages 4–7, respectively [40]. Pulmonary gas exchange will be measured from the beginning of the rest period until the end of the test using a metabolic system (Parvo TrueOne 2400, ParvoMedics Inc., East Sandy, UT, USA or MetaMax3B, Cortex Biophysik, GmbH, Leipzig, Germany). Prior to the test, participants will be asked to avoid exercise, caffeine, and tobacco for 24 h and food for 2 h but to take all the usual medications. In accordance with Taylor et al. (2017) [41], VO_2_peak will be determined from the average of the two highest values attained in 10 s periods, disregarding outliers when the difference between the two highest VO2 values is greater than 200 mL/min divided by the participant’s body weight. Additionally, an electrocardiogram recording will be taken during the rest period and during the test. Endothelial parameters, such as systolic and diastolic blood pressure and heart rate, will be recorded during the rest period and during the 1 min and 5 min post tests. Work parameters, such as the protocol stages performed, the maximum velocity and gradient reached, the test duration, and the reason for ending it will also be recorded.

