#### 2.4.2. Heart Rate Variability

Taking into account the sample characteristics, we propose that the HRV be measured over a 60 s period with the subject lying down at rest just prior to the training session. This procedure, modified from Plews et al. (2017) [42], will allow the multidisciplinary team to manage data recording, maintaining the same conditions and position, thus obtaining more reliable data [43]. The HRV4Training smartphone application will be used. This tool was validated by Plews et al. (2017) [42] and employed in several studies, as it facilitates data measurements, providing either temporal (rMSSD, pNN50, and SDNN) or frequential (LF and HF) measurements using photoplethysmography. Data can be downloaded directly to a computer in the form of an Excel sheet.

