## Figures and Tables

**Figure 1 ijerph-19-10868-f001:**
[figure not shown]
HRV-guided training schema [36]. When LnrMSSD7-d is within the normal range, high-intensity training sessions will be prescribed. If LnrMSSD7-d falls below the normal range, low intensity or rest will be prescribed. Low = exercise at 65% of maximal heart rate, High = exercise at 85% more of maximal heart rate, Rest = resting day, HRV+ = increased or unchanged HRV; HRV− = decreased HRV.

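### HRV, the outcome of secondary aim (i), is timed only as pre-session readings that also steer the HRV-G load, so a late arm difference cannot separate lasting adaptation from short-term unloading

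*Protocol article*

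**What the plan says.** Secondary aim (i), at the end of the Introduction, is "to determine the effect of HIIT training compared to HRV-guided training on heart rate variability scores in post-stroke patients". Hypothesis (i) expects HRV to improve in both arms and to improve more under HRV guidance.

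HRV is also the control variable of one arm. Section 2.3 says "The training prescribed to the HRV-G group will depend on the subjects’ daily HRV", and the Figure 1 legend adds "If LnrMSSD7-d falls below the normal range, low intensity or rest will be prescribed". HIIT-G follows Table 1 whatever its HRV.

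On timing, section 2.4 says "Heart rate variability, exercise adherence, feasibility, and safety will be recorded daily during the intervention by the physical exercise graduate". Section 2.4.2 specifies a 60 s reading "with the subject lying down at rest just prior to the training session". The same paragraph of section 2.4 gives other outcomes a window outside the programme: "The treadmill test and blood sample collection will be carried out by the cardiologist one week before and after the intervention". HRV is not among them. Section 2.4.1 mentions a resting ECG at the treadmill test, but does not say that HRV is derived from it.

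Section 2.8 compares the arms by ANCOVA on the post-test value, adjusted for baseline and age. It does not say which HRV reading is the post-test.

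**The concern.** One reading does two jobs: it decides the next load in HRV-G, and it is the recorded outcome. Late in the programme the arms are under different loads, and in HRV-G the load is lowered precisely when the reading is low. If recent load depresses the next reading, the rule pulls HRV back up in one arm and nothing does so in the other. A higher late value in HRV-G could then reflect lasting autonomic adaptation, short-term unloading, or a mixture.

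The Introduction presents HRV as a measure of cardiovascular response to therapy and cites a rise in basal HRV after HIIT, so readers are likely to take the aim (i) result as adaptation. At stake is the interpretation of one secondary outcome, not the primary VO2peak comparison.

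**Working it through.** **Step 1: which readings carry arm-specific load.** Table 1 has 24 sessions: 6 in the familiarization period (weeks 1–2) and 18 in the training period (weeks 3–8). Section 2.3 says "The FP will be common to both groups". A reading taken before session *k* reflects sessions 1 to *k* − 1.

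- Before sessions 1–7, only common sessions have taken place: 7 readings without arm-specific load.
- Before sessions 8–24, at least one arm-specific session has taken place: 24 − 7 = 17 readings.

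A clean baseline therefore exists. A follow-up reading free of recent arm-specific load does not appear in the text. In weeks 7–8 the HIIT-G work intervals are at 95–100% max HR.

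**Step 2: how large the unloading component could be.** The documents give no between-session carry-over. The Introduction cites only that HRV falls with exercise in stroke patients and has not recovered within 30 min. The following simulation is therefore illustrative, and all its inputs are assumptions:

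- The total SD of one HRV reading is 1 and the within-person correlation is 0.6 (variance 0.6 between patients, 0.4 within).
- Reading = patient mean + noise − *c* if the preceding session was a high-intensity training-period session. Low and familiarization sessions leave no carry-over.
- HIIT-G is always high in sessions 7–24. HRV-G is low when the mean of the last three readings falls below the familiarization mean minus 0.5 within-person SD.
- The endpoint is the mean of the readings before sessions 22–24.
- Neither arm has any lasting adaptation.

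The late difference should be close to *c* × the share of HRV-G sessions turned low:

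| *c* (SD) | share low | *c* × share | simulated late difference (SD) | off-programme difference (SD) |
|---|---|---|---|---|
| 0 | 0.251 | 0 | 0.00 | 0.00 |
| 0.1 | 0.292 | 0.029 | 0.03 | 0.00 |
| 0.25 | 0.353 | 0.088 | 0.09 | 0.00 |
| 0.5 | 0.446 | 0.223 | 0.23 | 0.00 |
| 1.0 | 0.580 | 0.580 | 0.60 | 0.00 |

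The off-programme column assumes that carry-over has gone by one week after the programme.

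**Step 3: can the two sources be told apart?** Let a lasting effect in HRV-G build up linearly over sessions 7–24.

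| lasting effect (SD) | *c* (SD) | late in-programme difference (SD) | off-programme difference (SD) |
|---|---|---|---|
| 0.2 | 0 | 0.19 | 0.20 |
| 0.1 | 0.25 | 0.17 | 0.10 |
| 0 | 0.5 | 0.23 | 0.00 |

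With 30 per arm, the standard error of a difference between single readings, without baseline adjustment, is √(2/30) = 0.26 SD. The three in-programme results (0.17 to 0.23) are indistinguishable. The expected off-programme values (0.20, 0.10, 0.00) follow the lasting effect, although a trial of this size would not separate these small values either. The gain is in what the endpoint measures, not in power.

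**The case against.** The case on the other side has real force.

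- **The randomised contrast is valid.** Aim (i) speaks of HRV scores. Unloading on low HRV is the assigned treatment, so its effect on those scores is part of the strategy's effect. A reader might infer that using the trigger as an outcome invalidates the comparison. It does not: with *c* = 0 the difference in step 2 is 0.00. Only the reading of it as lasting adaptation is limited.
- **Carry-over may be small.** With three sessions a week, evenly spaced, the gap is 7/3, or about 2.3 days, and the documents cite nothing beyond 30 min. At *c* = 0.1–0.25 the artefact is 0.03–0.09 SD, small against 0.26. This stands: the size is unknown.
- **The sign of the overall result is open.** A reader might infer that HRV-G must win by construction. The Introduction itself cites increased basal HRV after HIIT, so HIIT-G could end higher. Only the unloading component has a predictable direction, and only if load lowers the next reading.
- **Not every reading is affected.** A reader might infer that no HRV value is free of arm-specific load. Step 1 shows that the first seven are.
- **Other outcomes are also read on the programme.** Function, body composition, quality of life and cognition are recorded in its last week. True, but none of them steers the load.
- **Part of the schedule is not visible.** Figure 2 is not shown, and the HRV procedure is deferred to a cited article. An off-programme reading could be listed there. What can be said is that sections 2.4 and 2.4.2 give none, while section 2.4 does give such a window to other measures.

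**Conclusion.** The point holds as a limit on interpretation. As the text times it, follow-up HRV consists of readings taken on the programme, and the 17 before sessions 8–24 mix any lasting adaptation with recent arm-specific load. How much they mix depends on a carry-over the documents do not give: 0.00 to 0.60 SD in favour of HRV-G for assumed values of 0 to 1.0 SD, under the simulation's simplified rule. The documents do not support saying that the comparison is biased by construction or that the HRV data are unusable. The in-programme difference answers what the strategy does to HRV while patients train under it. It does not answer whether resting autonomic function has changed in a way that outlasts the load. This is a cheap improvement to one secondary endpoint.

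**What to change.** In sections 2.4 and 2.4.2, add a supine 60 s resting reading in both arms, before the treadmill test, at the two visits already scheduled a week either side of the programme. Fix the same app and position as for the pre-session readings. The ECG taken at that visit is not an interchangeable substitute as described, since section 2.4.1 gives neither its position nor its duration. Name this reading as the aim (i) endpoint for resting HRV adaptation and enter it in the section 2.8 ANCOVA, with the pre-programme reading as the baseline covariate. Section 2.4.1 already asks patients to avoid exercise, caffeine and tobacco for 24 h beforehand, which helps standardise the reading.

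Keep the pre-session readings for guidance, unchanged, and report them by arm as on-treatment HRV, not as evidence of lasting adaptation. If Figure 2 already lists HRV at these visits, align the two sections with it.

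The cost is about one minute at each of two existing visits and a sentence in each section; the training rule is untouched. The downside is that one reading per visit is noisier than an average of several and may be affected by anticipation of the test.

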#### 2.4.1. VO_2peak_

In accordance with the Spanish Cardiology Society, a modified version of the Bruce protocol will be used as the treadmill test, as it is indicated for elderly people and those considered high risk. Unlike the Bruce protocol, in the modified version, stage 1 starts at a 0% gradient, walking at 45.5 m/min. During stages 2 and 3 (at 3′ and 6′), the percentage gradient increases by 5% each time. Therefore, 6′ more exercise is performed at low intensity. From there, the percentage gradient will increase by 2% every 3′, and the walking speeds will be 67 m/min, 91 m/min, 112.5 m/min, and 136.8 m/min in Stages 4–7, respectively [40]. Pulmonary gas exchange will be measured from the beginning of the rest period until the end of the test using a metabolic system (Parvo TrueOne 2400, ParvoMedics Inc., East Sandy, UT, USA or MetaMax3B, Cortex Biophysik, GmbH, Leipzig, Germany). Prior to the test, participants will be asked to avoid exercise, caffeine, and tobacco for 24 h and food for 2 h but to take all the usual medications. In accordance with Taylor et al. (2017) [41], VO_2_peak will be determined from the average of the two highest values attained in 10 s periods, disregarding outliers when the difference between the two highest VO2 values is greater than 200 mL/min divided by the participant’s body weight. Additionally, an electrocardiogram recording will be taken during the rest period and during the test. Endothelial parameters, such as systolic and diastolic blood pressure and heart rate, will be recorded during the rest period and during the 1 min and 5 min post tests. Work parameters, such as the protocol stages performed, the maximum velocity and gradient reached, the test duration, and the reason for ending it will also be recorded.

#### 2.4.2. Heart Rate Variability

Taking into account the sample characteristics, we propose that the HRV be measured over a 60 s period with the subject lying down at rest just prior to the training session. This procedure, modified from Plews et al. (2017) [42], will allow the multidisciplinary team to manage data recording, maintaining the same conditions and position, thus obtaining more reliable data [43]. The HRV4Training smartphone application will be used. This tool was validated by Plews et al. (2017) [42] and employed in several studies, as it facilitates data measurements, providing either temporal (rMSSD, pNN50, and SDNN) or frequential (LF and HF) measurements using photoplethysmography. Data can be downloaded directly to a computer in the form of an Excel sheet.

#### 2.4.3. Functional Performance

To measure functional capacity, the battery of tests included in the Senior Fitness Test [44] will be used, as these have been employed in previous studies on older people in which a program based on high-intensity training was implemented [9]. The following variables will be assessed: (a) static equilibrium by means of the monopodal equilibrium test; (b) the strength of the upper body with a bicep curl test; (c) the strength of the lower train using a test involving getting up from a chair and sitting; (d) agility with the timed-up and go (TUG) test; (e) gait speed, involving a test walking for 10 m; and (f) cardiorespiratory fitness with the 6 min walk test.

#### 2.4.4. Relative Weight and Body Fat Distribution Measures

Height will be measured using a measuring rod (Seca 213), and the body mass index (BMI) will be calculated according to the following formula: BMI = kg/m^2^. As body fat distribution can vary substantially and considering that abdominal adiposity has been associated with coronary heart disease [45,46], the waist-to-hip ratio will be measured according to the International Society for the Advancement of Kinanthropometry Standards [47]. The waist-to-height ratio will also be measured because recent systematic reviews with meta-analyses proposed this measure as a predictor of cardiovascular risk factors [48].

#### 2.4.5. Quality of Life

The MacNew QLMI post-myocardial infarction questionnaire will be completed. The questionnaire includes 27 specific items assessing the quality of life of patients who have suffered a myocardial infarction. The validated Spanish version of the MacNew QLMI will be used, which has demonstrated good reproducibility and internal consistency [49], preserving the “emotional”, “physical”, and “social” dimensions in its last modification [50].

#### 2.4.6. Blood Analysis

Following the Taylor et al. (2017) [41] protocol, blood analysis will include the lipid profile, detection and quantification of plasma insulin and its resistance, assessment of C-reactive protein, and inflammatory adipokines (leptin, adiponectin, tumor necrosis factor-a, interleukin-6, and appetite hormones).

#### 2.4.7. Cognitive Function

To determine brain function, several test will be used: (i) the Almeria spatial memory recognition test (ASMRT), a simple virtual-reality-based task for specific populations, such as older adults, that has a proven sensitivity to gender differences [51]; (ii) the virtual version of the Walking Corsi test (VR_WalCT) to measure topographical memory, given that [52] its equivalency to the real environment version has been proven; and (iii) the trail-making test (TMT) described by Bowie and Harvey (2006) [53] to detect neurological disease and neuropsychological impairment through the cognitive domains of processing speed, sequencing, mental flexibility, and visual motor skills.

#### 2.4.8. Exercise Adherence, Feasibility, and Safety

Adherence will be assessed by the number of sessions completed by the participants. At least 80% of sessions should be completed to consider adherence successful. Feasibility will be considered compliance with the exercise protocol and will be recorded as the percentage of participants that finish every training session. Safety will be measured as the number of adverse events occurring during the training sessions. In accordance with Villelabeitia-Jaureguizar et al. (2017) [54], these will be recorded as mild, moderate, or severe. Moreover, their relation to the exercise session will also be taken into account. All these variables will be recorded by the multidisciplinary group present at the exercise sessions.

The time schedule for enrolment, interventions, and assessments is shown in Figure 2.

